### 7.3. Other healthcare costs and informal care

Healthcare costs and informal care costs after clinical rehabilitation will be collected through online administration of an adaptation of the iMTA Medical Consumption Questionnaire (iMCQ) at 6- and 12-months post stroke. Extrapolation will be used to calculate costs between 6- and 9-months post-stroke, as those data are not available due to a recall period of 3 months. The iMCQ will be used to measure all direct medical costs (consultations, hospitalizations), and direct non-medical costs (family care). Healthcare resource use will be multiplied with Dutch unit costs to determine healthcare costs. Unit

costs will be based on tariffs of the Dutch Healthcare Authority and/or as described in the Dutch Costing guideline.

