### **Costs**

The costs of the intervention are subdivided into direct medical costs, costs for patients and families, and productivity costs. Medical costs include the costs of the intervention/procedure itself, costs of clinical and outpatient rehabilitation and other medical costs, such as hospitalizations or first-line physical therapy. These costs are described in section 6.1 to 6.3. Informal care and productivity costs are described in section 6.4.

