## 8. Questionnaires

The Dutch versions of the iMTA Medical Consumption Questionnaire and the iMTA Productivity Cost Questionnaire are adapted to the B-STARS2 study population. The questionnaires are sent out digitally using an online platform to capture research data for clinical trials (CASTOR). The digital questionnaires are constructed to hide irrelevant questions based on previous answers, minimizing the survey completion time and increasing the response rate. The list of questions in the questionnaires is shown in Appendix A.

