## 10. References

## Appendix A

### Vragenlijst Zorggebruik

De vragen in deze vragenlijst gaan over uw zorggebruik sinds uw ontslag uit het revalidatiecentrum. Deze gegevens gebruiken we om te bepalen of TMS-behandeling leidt tot een vermindering van zorgkosten doordat patiënten mogelijk sneller herstellen, en daardoor minder zorg nodig hebben. Nadat u een vraag heeft beantwoord verschijnen er 3 puntjes naast de vraag. Door op de 3 puntjes te klikken verschijnt de optie om uw antwoord op een vraag te wissen.

De vragen in deze vragenlijst gaan over de zorg die u heeft ontvangen in de afgelopen 3 maanden.

- Bent u ontslagen uit het revalidatiecentrum? Dat wil zeggen: is uw klinische opnameperiode beëindigd?
- Op welke datum bent u ontslagen uit het revalidatiecentrum? Het gaat hierbij om de datum waarop de klinische opname is beëindigd. Het is mogelijk dat u na het ontslag nog voor poliklinische revalidatie in het revalidatiecentrum bent geweest.

De volgende vraag gaat over poliklinische revalidatie en zorg uit de eerste lijn. Poliklinische revalidatie vindt plaats in een revalidatiecentrum of een ziekenhuis, onder begeleiding van een revalidatieteam bestaande uit o.a. een revalidatiearts, fysiotherapeut, ergotherapeut en een maatschappelijk werker. Behandeling uit de 1ste lijn vindt plaats in een fysio- of ergotherapiepraktijk, onder begeleiding van een fysio- of ergotherapeut.

- Heeft u in de afgelopen 3 maanden poliklinische revalidatiebehandeling of therapie uit de 1ste lijn ontvangen in verband met uw beroerte?
- Welke situaties zijn op u van toepassing geweest in de afgelopen 3 maanden? U kunt meerdere opties selecteren.
  - Ik heb poliklinische revalidatiebehandeling gehad in een revalidatiecentrum of ziekenhuis
  - Ik heb therapie uit de 1ste lijn bij een fysio- of ergotherapiepraktijk gehad.

- Ontvangt u de poliklinische revalidatiebehandeling in hetzelfde centrum als waar u klinische revalidatiebehandeling heeft gehad?

De volgende vragen gaan alleen over behandelingen die u heeft ontvangen uit de 1ste lijn.

Heeft u geen afspraken gehad, vul dan 0 in.

- Hoeveel afspraken had u in de afgelopen 3 maanden met een maatschappelijk werker in de 1ste lijn?
- Hoeveel afspraken had u in de afgelopen 3 maanden met een fysiotherapeut in de 1ste lijn?
- Hoeveel afspraken had u in de afgelopen 3 maanden met een ergotherapeut in de 1ste lijn?
- Hoeveel afspraken had u in de afgelopen 3 maanden met een psycholoog in de 1ste lijn?

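### The care-use questionnaire defines first-line care too narrowly for its own psychologist and social-worker items, and does not measure all direct medical costs as the plan states

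*Combined protocol and SAP*

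**What the plan says.** The health-economic plan takes a societal perspective (sections 1.2 and 4.1). Section 2.4 sets the cost classes: "The costs of the intervention are subdivided into direct medical costs, costs for patients and families, and productivity costs". For care after inpatient rehabilitation, section 7.3 relies on an adapted iMCQ at 6 and 12 months: "The iMCQ will be used to measure all direct medical costs (consultations, hospitalizations), and direct non-medical costs (family care". Protocol section 8.1.2 (Cost-effectiveness) says the same.

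Section 8 of the health-economic plan makes Appendix A the item list: "The list of questions in the questionnaires is shown in Appendix A". It adds that the digital forms are "constructed to hide irrelevant questions based on previous answers".

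Appendix A (Vragenlijst Zorggebruik) explains first-line care to the patient: "Behandeling uit de 1ste lijn vindt plaats in een fysio- of ergotherapiepraktijk, onder begeleiding van een fysio- of ergotherapeut". A gate question asks about stroke-related outpatient rehabilitation or first-line therapy. Of the two answer options that follow, the first-line one reads "Ik heb therapie uit de 1ste lijn bij een fysio- of ergotherapiepraktijk gehad". The visit counts are introduced with "De volgende vragen gaan alleen over behandelingen die u heeft ontvangen uit de 1ste lijn", and they include "Hoeveel afspraken had u in de afgelopen 3 maanden met een psycholoog in de 1ste lijn" and a matching item for a social worker.

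**The concern.** There are two separate defects.

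The first is a mismatch inside the questionnaire. By the definition given, a patient whose only community care was from a psychologist or social worker has had no first-line treatment. A literal reader can truthfully answer no at the gate, or enter 0 further down. A 0 entered in error counts as observed data, so the multiple imputation planned for missing data would not repair it. Section 7.3 also extrapolates to the months between 6 and 9, so an under-report in a measured window can carry into the window that is filled in.

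The second is scope. The claim covers all direct medical costs, but some kinds of medical cost have no item. The reported societal cost would then be narrower than the plan says. The budget impact analysis (section 5), which extrapolates these results and takes an insurer perspective among others, would inherit the same gap.

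**Working it through.** No arithmetic in the plan bears on this point. The check sets the questionnaire beside the claim, item by item.

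**Step 1: the first-line block.** The definition names two settings and two professions, both physiotherapy or occupational therapy. The four counts compare with it as follows.

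| Visit count asked | Inside the definition? |
|---|---|
| Social worker | No |
| Physiotherapist | Yes |
| Occupational therapist | Yes |
| Psychologist | No |

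So 2 of 4 counts fall outside the definition that governs them. The same introduction names the social worker as a member of the outpatient rehabilitation team, which points patients further away from reporting such visits as first-line.

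**Step 2: can a later item recover these visits?** The block on other care asks about the GP, practice nurse, company doctor, emergency department, ambulance and hospital outpatient doctors. Its one open item is limited to doctors. None of these would pick up a community psychologist or social worker.

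**Step 3: coverage of the whole care-use questionnaire.** Counting the bulleted questions: 2 on discharge, 3 on outpatient or first-line care, 4 visit counts, 7 on other providers, 3 on hospital admission, 3 on home care, 2 on day treatment, 2 on care-home stay and 3 on informal care. That is 2 + 3 + 4 + 7 + 3 + 3 + 2 + 2 + 3 = 29.

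| Category | Items out of 29 | Other follow-up source in the documents |
|---|---|---|
| Speech therapy | 0 | Possibly within outpatient rehabilitation (section 7.2) |
| Medication | 0 | None; current medication is a baseline value only (protocol 8.1.3) |
| Aids and home adaptations | 0 | None |
| Ambulance | 1 | Not needed |
| Relatives' help, including transport | 3 | Not needed |

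**Step 4: what could be lost.** Let f be the share of first-line psychologist and social-worker visits that goes unreported because of the definition. The measured cost for those providers is (1 − f) times the true cost. The documents do not narrow f within 0 to 1. If everyone sees the items and answers them as named, f = 0. If the gate hides them, f is the share of those visits made by patients who answered no.

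**Step 5: the between-arm difference.** The reported cost difference omits (unmeasured cost, active) − (unmeasured cost, sham). This is zero if the unmeasured categories cost the same in both arms, and otherwise equals their difference. The documents give no cost for either arm.

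**The case against.** The best defence of the wording is that the bracket after the word all, naming consultations and hospitalizations, states the intended scope. Medication and aids would then never have been claimed. That is a fair reading, but it does not rescue the sentence: visits to a community speech therapist, psychologist or social worker are consultations, and the first has no item while the other two sit under a definition that excludes them.

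Section 7.2 costs outpatient rehabilitation as duration times daily cost, so therapy delivered inside such a programme need not be counted item by item. This stands and limits the gap. It does not reach first-line care or medication, and the data exist only for patients who stay with the same centre, with imputation for the rest.

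The first-line items name the provider plainly, so a patient who sees them may simply answer correctly. This also stands. Under-reporting is possible, not demonstrated.

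The questionnaire was deliberately adapted and kept short to protect the response rate (sections 2.6 and 8). That weighs against insisting on new items, but not against correcting a definition or a sentence.

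A reader might go further and infer that travel is a missing direct medical cost. The documents do not support this. Section 2.4 keeps patient and family costs apart from medical costs, and the only content it names for that class is informal care. Ambulance use is asked, and being taken somewhere by relatives counts as informal care in Appendix A. Paid travel is at most a gap in the societal perspective.

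**Conclusion.** The point holds for two things. The first-line definition and gate option contradict the items they govern, so psychologist and social-worker visits may be under-reported. The statement that the iMCQ measures all direct medical costs is not met, because speech therapy, medication, and aids and home adaptations have no item.

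The extent is 2 of 4 first-line counts and three cost categories with 0 of 29 items. No monetary size follows from the documents. The conclusion assumes that Appendix A is the complete list, as section 8 says.

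Three stronger conclusions may suggest themselves, and the documents support none of them. One is that these visits are certain to be undercounted: the branching rules are not shown, and the effect of the definition on answers is an inference. Another is that every missing category is zero for every patient: rehabilitation costing may include some speech therapy. The third is that the comparison of arms is biased: both arms answer the same form, and no source shows that the unmeasured costs differ, or that they do not.

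The point concerns a secondary health-economic analysis and leaves the primary efficacy and safety analyses untouched. It is worth acting on because the repair is nearly free and changes both the data collected and what the cost result can claim.

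**What to change.** 1. In Appendix A, reword first-line care as care given outside a rehabilitation centre or hospital by a physiotherapist, occupational therapist, psychologist or social worker (and speech therapist, if counted), and change the first-line answer option to match. Alternatively, put the visit counts to everyone. In that case, say in the items whether only stroke-related visits count, since that limit now sits in the gate question.
2. State the branching rules in section 8 of the health-economic plan.
3. In section 7.3 and in protocol section 8.1.2, replace the claim of all direct medical costs with the categories measured and those left out.
4. Optional: add short items on speech therapy, medication, and aids or home adaptations.

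Steps 1 to 3 cost one definition, one answer option and a few sentences, with the amendment notified as protocol section 12.3 requires. Step 4 lengthens the questionnaire slightly, and early respondents will have no such data. Early respondents will also have answered under the narrow definition, so record the date of the change and report the psychologist and social-worker counts before and after it.

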## 7.4. Productivity costs

Productivity losses for individual patients will be collected using online administration of an adaptation of the iMTA Productivity Cost Questionnaire (iPCQ) at 6- and 12-months post-stroke. The iPCQ adaptation consists of two modules: lost productivity at paid work due to absenteeism and lost productivity at paid work due to presenteeism. Extrapolation will be used to calculate costs between discharge and 5 months and 6- and 11-months post-stroke, as those data are not available due to a recall period of 4 weeks.

## 8. Questionnaires

The Dutch versions of the iMTA Medical Consumption Questionnaire and the iMTA Productivity Cost Questionnaire are adapted to the B-STARS2 study population. The questionnaires are sent out digitally using an online platform to capture research data for clinical trials (CASTOR). The digital questionnaires are constructed to hide irrelevant questions based on previous answers, minimizing the survey completion time and increasing the response rate. The list of questions in the questionnaires is shown in Appendix A.

## 9. Change log

| Version | Changes                                                                                                                                                                                                                                                            | Date       |
|---------|--------------------------------------------------------------------------------------------------------------------------------------------------------------------------------------------------------------------------------------------------------------------|------------|
| 2       | 

- Changed the time horizon of the primary analysis

- Added the EQ-5D at 6 months post-stroke

- Added an assumption on the change in quality of life between stroke onset and 12 months post-stroke

 | 14-10-2024 |

## 10. References

## Appendix A

### Vragenlijst Zorggebruik

De vragen in deze vragenlijst gaan over uw zorggebruik sinds uw ontslag uit het revalidatiecentrum. Deze gegevens gebruiken we om te bepalen of TMS-behandeling leidt tot een vermindering van zorgkosten doordat patiënten mogelijk sneller herstellen, en daardoor minder zorg nodig hebben. Nadat u een vraag heeft beantwoord verschijnen er 3 puntjes naast de vraag. Door op de 3 puntjes te klikken verschijnt de optie om uw antwoord op een vraag te wissen.

De vragen in deze vragenlijst gaan over de zorg die u heeft ontvangen in de afgelopen 3 maanden.

- Bent u ontslagen uit het revalidatiecentrum? Dat wil zeggen: is uw klinische opnameperiode beëindigd?
- Op welke datum bent u ontslagen uit het revalidatiecentrum? Het gaat hierbij om de datum waarop de klinische opname is beëindigd. Het is mogelijk dat u na het ontslag nog voor poliklinische revalidatie in het revalidatiecentrum bent geweest.

De volgende vraag gaat over poliklinische revalidatie en zorg uit de eerste lijn. Poliklinische revalidatie vindt plaats in een revalidatiecentrum of een ziekenhuis, onder begeleiding van een revalidatieteam bestaande uit o.a. een revalidatiearts, fysiotherapeut, ergotherapeut en een maatschappelijk werker. Behandeling uit de 1ste lijn vindt plaats in een fysio- of ergotherapiepraktijk, onder begeleiding van een fysio- of ergotherapeut.

- Heeft u in de afgelopen 3 maanden poliklinische revalidatiebehandeling of therapie uit de 1ste lijn ontvangen in verband met uw beroerte?
- Welke situaties zijn op u van toepassing geweest in de afgelopen 3 maanden? U kunt meerdere opties selecteren.
  - Ik heb poliklinische revalidatiebehandeling gehad in een revalidatiecentrum of ziekenhuis
  - Ik heb therapie uit de 1ste lijn bij een fysio- of ergotherapiepraktijk gehad.

- Ontvangt u de poliklinische revalidatiebehandeling in hetzelfde centrum als waar u klinische revalidatiebehandeling heeft gehad?

De volgende vragen gaan alleen over behandelingen die u heeft ontvangen uit de 1ste lijn.

Heeft u geen afspraken gehad, vul dan 0 in.

- Hoeveel afspraken had u in de afgelopen 3 maanden met een maatschappelijk werker in de 1ste lijn?
- Hoeveel afspraken had u in de afgelopen 3 maanden met een fysiotherapeut in de 1ste lijn?
- Hoeveel afspraken had u in de afgelopen 3 maanden met een ergotherapeut in de 1ste lijn?
- Hoeveel afspraken had u in de afgelopen 3 maanden met een psycholoog in de 1ste lijn?

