## **8. METHODS**

### **8.1 Study parameters/endpoints**

#### **8.1.1 Main study parameter/endpoint**

The primary endpoint is the upper extremity section of the Fugl-Meyer assessment (FM-UE) at 90 days post-stroke. The FM-UE assesses upper limb motor impairment on a scale from 0 to 66 points, with a higher score indicating less impairment. The FM-UE will be assessed by certified assessors. Before certification, assessors will receive on-site training by the team of coordinating investigators and must successfully complete an FM-UE exam. See section 8.3.

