## 8.3 Study procedures

A local investigator will perform screening and the informed consent procedure described in section 11.1. After written informed consent is obtained, baseline assessments will be performed. Baseline assessment duration is up to 90 minutes. Descriptions of the study procedures to determine the outcome measures (Table 1) are provided below.

After the baseline assessments, patients undergo the intervention described in section 5.1. The following data related to cTBS treatment is acquired: date and time of each treatment, the resting motor threshold, experienced side-effects and the number of minutes of upper limb therapy after the previous session. At the end of treatment course, the following data is acquired: the number of completed treatments,

the duration of the treatment course in days, and whether the patient thinks he/she received active or sham treatment.

At 90 days and 12 months post-stroke, the outcome measures described in table 1 are reassessed. Follow-up assessment duration is up to 90 minutes per follow-up. Detailed descriptions of these tests are provided below.

After the patient has been discharged, the total amount of upper limb therapy received during clinical rehabilitation and the length of stay at the rehabilitation center are acquired.

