## 3. Study design

B-STARS2 is a multi-centre, double-blind, randomized, sham-controlled, clinical trial. Participants will be recruited from 16 rehabilitation centres in the Netherlands over a period of 51 months (Q2 of 2024 to Q4 of 2028). The total duration of follow-up for each participant is until one year after stroke. The total study duration is 63 months.

The intervention consists of ten daily sessions of active or sham cTBS, delivered over the contralesional primary motor cortex, started within 21 days post-stroke and combined with regular care upper limb therapy.

The cost-utility analysis will be performed alongside the B-STARS2 trial. During the trial, data on patient-reported medical consumption and productivity losses will be acquired through digital questionnaires at 6- and 12-months post-stroke and quality of life will be assessed at 3- and 12-months post-stroke (Figure 1).

[figure not shown]

**Figure 1.** Study timeline.

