## 6. Effects

Quality of life will be assessed with the EQ-5D-5L, within 3 weeks after stroke and at 3-, 6- and 12-months post-stroke. Quality of life is assessed at 3 and 6 months post-stroke, when most patients will have completed clinical rehabilitation. Quality of life will be assessed again at one-year post-stroke, when recovery has plateaued, and most patients will have ceased rehabilitation and reintegrated into society. Quality of life is assumed to increase logarithmically between stroke onset and 12 months post-stroke based on existing data from our phase II RCT, B-STARS. QALYs will be assessed by combining mortality and quality of life using an area-under-the-curve approach. The Dutch tariffs will be used to convert the EQ-5D-5L scores into a utility score. This utility score ranges from 0 to 1, in which 0 corresponds to death and 1 corresponds to perfect health.

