### **Vragenlijst productiviteit**

De vragen in deze vragenlijst gaan over betaald werk dat u deed voor de beroerte, en over eventuele terugkeer naar werk. Deze gegevens gebruiken we om te bepalen of TMS-behandeling leidt tot een vervroegde terugkeer naar werk.

De volgende vragen gaan over betaald werk.

- Verrichtte u voor uw beroerte betaald werk?
- Hoeveel uur per week werkte u?
- Op hoeveel dagen in de week werkte u?
- Heeft u de afgelopen 4 weken betaald werk verricht? Het gaat hierbij ook om werk in het kader van re-integratie.
- Wanneer bent u (weer) begonnen met betaald werk?
- Doet u hetzelfde werk als voor uw beroerte?
- Hoeveel uur per week heeft u betaald werk verricht in de afgelopen 4 weken? Het gaat hierbij om het gemiddeld aantal uur per week dat u betaald werk heeft verricht. Het aantal uren dat u afwezig bent geweest door re-integratie of ziekte tellen niet mee.
- Waren er in de afgelopen 4 weken dagen waarop u wel gewerkt heeft maar tijdens uw werk last had van de gevolgen van uw beroerte?

- Op hoeveel werkdagen had u tijdens uw werk last van de gevolgen van uw beroerte in de afgelopen 4 weken? Tel alleen de werkdagen bij elkaar op.
- Op de dagen dat u last had, kon u misschien niet zoveel werk doen als normaal. Hoeveel werk kon u op deze dagen gemiddeld doen op een schaal van 0 tot 10?

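### Both cost questionnaires disclose the study hypothesis, in its favourable direction only, immediately before patients report their care use and work

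*Combined protocol and SAP*

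**What the plan says.** Appendix A of the health-economic plan reproduces the two patient questionnaires in Dutch.

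- **Care use (Vragenlijst Zorggebruik).** The introduction says that the data are used "om te bepalen of TMS-behandeling leidt tot een vermindering van zorgkosten doordat patiënten mogelijk sneller herstellen", and continues "en daardoor minder zorg nodig hebben". In English: to determine whether TMS lowers care costs because patients possibly recover faster and so need less care.
- **Productivity (Vragenlijst productiviteit).** The introduction says "Deze gegevens gebruiken we om te bepalen of TMS-behandeling leidt tot een vervroegde terugkeer naar werk". In English: the data are used to determine whether TMS leads to an earlier return to work.

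On timing, section 3 of the health-economic plan states that "data on patient-reported medical consumption and productivity losses will be acquired through digital questionnaires at 6- and 12-months post-stroke". Protocol section 8.1.2 gives the same two time points.

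At the end of the treatment course the trial also records "whether the patient thinks he/she received active or sham treatment" (protocol section 8.3). SAP sections 5 to 7 plan no analysis of that guess.

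**The concern.** An introduction that names the hoped-for answer can act as a prompt. A patient who believes the treatment was active, and has just read that it may mean less care and earlier work, may report somewhat less of the one and more of the other. Some items leave room for this: help received because of the stroke, working days troubled by its consequences, and work output on a 0 to 10 scale.

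These answers carry weight in the societal cost result because they are stretched over time. Under health-economic plan section 7.3, a three-month recall is extrapolated to cover months 6 to 9. Under section 7.4, a four-week recall is extrapolated to cover discharge to month 5 and months 6 to 11. A shift in reporting would pass into those totals, and from there into the decision model (section 4.1) and the budget impact analysis (section 5). The direction named in the introductions is not needed to answer any of the items.

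**Working it through.** The plan states no figure on this point, so there is none to reproduce. The check has three parts.

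**1. What the sentences assert.** Both use the Dutch for *to determine whether*, and the care-use text adds *possibly*. Neither says that an effect is expected. Both name only the favourable outcome; no neutral or opposite outcome is mentioned.

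**2. Which data are exposed.**

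| Data | Source and timing | Exposed? |
|---|---|---|
| Primary FM-UE | Performance test at 90 days, before the first form | No |
| ARAT, NHPT, later FM-UE | Performance tests | No |
| Inpatient length of stay | Centre administration (protocol 8.1.2) | No |
| Outpatient rehabilitation cost | Duration times the centre's daily cost, imputed if at another centre (health-economic plan 7.2) | Not in this way |
| Intervention cost | Bottom-up costing from centre finances and staff time (health-economic plan 7.1) | No |
| Other care use, informal care, productivity | Self-report on these forms | Yes |

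On the first row, protocol section 8.1.1 reads "The primary endpoint is the upper extremity section of the Fugl-Meyer assessment (FM-UE) at 90 days post-stroke".

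**3. What a prompt could do to the arm comparison.** Suppose patients who believe they had active treatment under-report cost by a fraction s. Let pA and pS be the shares with that belief in the active and sham arms, and mA and mS the true mean self-reported costs. Then

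observed difference = mA(1 − s·pA) − mS(1 − s·pS).

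*Unequal beliefs, no true difference (mA = mS = m).* The observed difference is −s·(pA − pS)·m, which favours cTBS when pA exceeds pS. The documents give neither s nor the belief shares, so all inputs here are assumptions. Shift as a percentage of m:

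| s | gap 0 points | 10 points | 20 points | 30 points |
|---|---|---|---|---|
| 5% | 0 | 0.5 | 1.0 | 1.5 |
| 10% | 0 | 1.0 | 2.0 | 3.0 |
| 20% | 0 | 2.0 | 4.0 | 6.0 |

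For example, beliefs of 65% and 45% give (0.65 − 0.45) × 0.10 = 2% and (0.65 − 0.45) × 0.20 = 4%.

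*Equal beliefs (pA = pS = p).* The expression becomes (1 − s·p)(mA − mS). Writing u = s·p for the common under-reporting, u of 5%, 10% or 20% leaves 95%, 90% or 80% of the true difference. That is attenuation, not bias towards cTBS.

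Two cautions apply to the table. It charges all under-reporting among believers to the introductory sentence, although belief could colour recall under neutral wording too; only the increment due to the sentence counts. It is also scaled to mean self-reported cost, which is only part of total cost, and the documents do not give that share.

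**The case against.** The strongest case against the point is that the forms ask an open question of blinded patients. The documents show one text for both arms. Blinding is to hold until the last patient's 12-month follow-up (protocol section 8.2), and the sham coil looks and sounds like the active one (protocol section 5.1). Most items ask for counts, dates, days or hours. Patients have already had the study explained and received an information letter (protocol section 11.2), which is not available here, so whether the sentence adds any expectation cannot be judged. Stating why data are collected is also an ordinary use of an introduction.

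Much of this stands, and it rules out three stronger readings that a reader might infer.

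- **That patients are told TMS is expected to help.** The text does not say so.
- **That the cost result is biased towards cTBS, by 2% to 4% or any other amount.** This needs beliefs to differ by arm. The documents do not show that they do; recording a guess is not evidence of a difference.
- **That all costs after discharge, or the 12-month outcomes in general, are affected.** Outpatient rehabilitation is costed from its duration and a centre rate, and the motor outcomes are performance tests. The 12-month SIS and EQ-5D-5L are self-reported and follow the 6-month form, but an effect of one sentence six months later is conjecture.

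What does not stand is the claim that blinding settles the matter. Equal beliefs at 6 and 12 months are assumed, not secured. The sham description covers look and sound but is silent on scalp sensation. If cTBS works, patients who recover well may infer that they had it. The guess is taken once, at the end of treatment, so later divergence would not be seen.

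**Conclusion.** The point holds as a modest, avoidable weakness in questionnaire wording. It is not an error in the analysis, and it leaves the primary endpoint untouched. Both introductions disclose the hypothesis in its favourable direction only, just before self-report of care use, informal care and productivity.

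The size is unknown. On assumed inputs, the between-arm shift is zero if beliefs are equal and reaches 6% of mean self-reported cost at the far corner of the range (30-point belief gap, 20% shift). These values attribute the whole reporting shift to the sentence, so if belief would also colour answers under neutral wording, the sentence's own contribution is smaller. With equal beliefs, the remaining risk is distorted absolute costs or an attenuated difference. The case for acting rests on the low cost of the change, not on a demonstrated bias.

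**What to change.** Replace the purpose sentence in each introduction with neutral text: for care use, that these questions map the care the patient used; for productivity, that they map the paid work the patient did. Mention neither TMS, faster recovery, lower costs nor earlier return to work. Leave every item unchanged.

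The cost is two sentences in the CASTOR forms and notification of changed patient-facing text to the ethics committee (protocol section 12.3 requires amendments to be notified). The downside is that answers before and after the change follow different introductions, so record the form version with each response. Because both arms are randomised concurrently within centre, the switch should fall evenly across arms and should not itself create a between-arm difference.

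As an optional addition, the SAP could pre-specify a table of the treatment guess by arm. The data are already collected, and the table would show whether beliefs differed at the end of treatment, though not at 6 or 12 months.
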